### Interventions

The treatment course is 28 days.

The control group will be given standard Western medicine therapy, including: routine monitoring of vital signs; blood, arterial blood gas, and biochemical analysis; coagulation monitoring; step-down antimicrobial therapy; handle the respiratory secretions; mechanical ventilation; liquid nutrient support; maintenance of blood sugar, acid base, and electrolyte balance; correct coagulation function; etc.

The trial group will receive standard Western medicine therapy plus *Buzhong Yiqi* decoction (*Radix Astragali seu Hedysari* 45 g, *Radix Codonopsis* 15 g, fried *Rhizoma Atractylodis Macrocephalae* 15 g, prepared *Radix Glycyrrhiza* 15 g, *Radix Angelicae Sinensis* 10 g, *Pericarpium Citri Reticulatae* 9 g, *Rhizoma Cimicifugae* 12 g, and *Radix Bupleuri* 20 g; NONG’s granular preparation, dissolved in 200 mL warm boiled water and taken orally or by nasal feed once daily).

### Outcome measures

#### Laboratory tests

In both groups laboratory tests will include routine blood, urine, and fecal tests, blood gas analysis, liver and kidney function, coagulation function, and lactic acid, C-reactive protein, and procalcitonin analysis.

### Primary outcome

#### Efficacy evaluation criteria in TCM

Evaluation criteria by clinical manifestations are in reference to the *Criteria of Diagnosis and Therapeutic Effect of Diseases and Syndromes in Traditional Chinese Medicine* (Chinese Medicine Industry Standards of the People’s Republic of China; ZY/T001.1–94):
Clinical control: After treatment, symptoms and signs almost disappear and patients return to normal activities and work. The efficacy rate for syndromes is ≥ 90%.Excellent efficacy: After treatment, symptoms and signs and the results of examinations improve significantly. The efficacy rate for syndromes is ≥ 60% but < 90%.Efficacy: After treatment, symptoms and signs and the results of examinations improve. The efficacy rate for syndromes is ≥ 30% but < 60%.Lack of efficacy: After treatment, symptoms and signs and the results of examinations do not improve compared to before treatment. The efficacy rate for syndromes is < 30%.

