### Secondary outcomes

Clinical pulmonary infection score (CPIS): CPIS is a comprehensive clinical and imaging standard to assess the severity of pulmonary infection. It includes the following indicators: body temperature, white blood cell count, tracheal secretions, oxygenation, X-ray pulmonary infiltration, and progress in etiology. The clinical pulmonary infection score is compared before and after treatment. The CPIS details can be found in Additional file 3. Evaluation of disease severity: the scores of patients in the two groups are compared using the APECHA II scoring system before and after treatment. Improvement rate in APECHA II score = (Post-treatment score − Pre-treatment score)/Pre-treatment score. The APECHAII details can be found in Additional file 2. Clearance of drug-resistant pathogens: observed on days 7, 14, 21, and 28.Comparison of mechanical ventilation time and success rate of weaning off the ventilator are calculated if appropriate.Comparison of mortality: mortality is compared on day 28 between the groups.Radiography indicators: pulmonary CT imaging results are compared between the groups before and after treatment.Number of hospitalization days: survival days of patients who die and hospitalization days of those who survive and are discharged.

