### Sample size

Considering that no previous studies have been conducted to calculate the sample size, and assuming that the withdrawal rate is less than 15% [23], we expect that 100 patients will be enrolled in each arm, and that the final sample size of each arm will be at least 85. The data we collect will be helpful to calculate the appropriate sample size in the future and provide reference for further large-scale research.

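### No rule says how deaths count in the primary TCM grade or in CPIS, APACHE II and CT, and the withdrawal rules point to a completer analysis that drops them

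*Protocol article*

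**What the plan says.** **Primary outcome** (Protocol article, Efficacy evaluation criteria in TCM). There are four ordered grades, each defined by the state after treatment and by a syndrome efficacy rate. The lowest is: "Lack of efficacy: After treatment, symptoms and signs and the results of examinations do not improve compared to before treatment", with a syndrome rate below 30%. Death is not mentioned in any grade.

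**Secondary outcomes** (same article, Secondary outcomes).
- CPIS: "The clinical pulmonary infection score is compared before and after treatment".
- APACHE II (spelt APECHA II in the article): "Improvement rate in APECHA II score = (Post-treatment score − Pre-treatment score)/Pre-treatment score".
- CT: "pulmonary CT imaging results are compared between the groups before and after treatment".
- Mortality is a separate outcome: "mortality is compared on day 28 between the groups".
- Hospitalization days is the only outcome other than mortality that says how deaths enter: survival days are used for patients who die.

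**Time frame** (Interventions): "The treatment course is 28 days".

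**Who leaves the trial** (Withdrawal/trial discontinuation/drop-out criteria). Criterion 2 covers incomplete data that cannot be analysed. Criterion 4 covers continuing deterioration, at the investigator's judgement. Criterion 6 classes patients who withdraw without completing the observation period as drop-outs.

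**Sample size.** With 100 enrolled per arm and a withdrawal rate below 15%, "the final sample size of each arm will be at least 85".

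**The concern.** The trial enrols patients with multi-drug-resistant hospital-acquired pneumonia from emergency departments and ICUs, and treats them for 28 days. Some will die before a post-treatment assessment. The plan recognises this by comparing day-28 mortality and by giving deaths a rule for hospitalization days. It gives no such rule for the primary grade or for the three before-and-after measures.

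The printed text leans towards leaving these patients out. A patient who dies early has incomplete data, has probably been deteriorating, and has not finished observation. These are the situations that criteria 2, 4 and 6 address, and the final sample is what remains after withdrawals.

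Death is the plainest treatment failure. If it leaves the denominator of the efficacy rate, the arms are compared among survivors, who are no longer a randomised comparison. An arm that loses more of its non-responders to death then shows a higher efficacy rate. An arm that keeps such patients alive shows a lower one. The primary result could point the wrong way with no error in the data.

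**Working it through.** **1. The plan's own figure.** 100 × (1 − 0.15) = 85 per arm, and 5 sites × 40 = 200 in total. Both reproduce. So the plan expects up to 15 patients per arm to leave the final sample. It does not say whether deaths are among them. If deaths are not counted as withdrawals and are also not evaluable, the figure of 85 fails once deaths and withdrawals together exceed 15 in an arm.

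**2. Inputs the documents do not give.** No mortality rate, response rate, score mean or SD is stated. All rates below are assumptions, chosen to show direction and range.

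**3. Primary outcome, equal true response, deaths only among non-responders.** Take 100 randomised per arm and 50 responders in each.
- All randomised, deaths counted as failures: 50/100 v 50/100 = 50% v 50%.
- Survivors only, deaths 20 v 30: 50/80 = 62.5% v 50/70 = 71.4%. The difference of 8.9 points favours the arm with more deaths.
- Read the other way round, the arm that loses 20 instead of 30 patients looks 8.9 points worse.
- Survivors only, deaths 15 v 15: 50/85 = 58.8% in both arms, so no distortion.

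Range with 40 to 60 responders per 100:

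| Deaths per 100 | Survivor-only difference favouring the arm with more deaths |
|---|---|
| 10 v 15 | 2.6 to 3.9 points |
| 10 v 20 | 5.6 to 8.3 points |
| 20 v 30 | 7.1 to 10.7 points |
| 20 v 35 | 11.5 to 17.3 points |

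In 100,000 simulated trials per setting (100 per arm, chi-square without continuity correction, two-sided 5%), the survivor-only test was significant in favour of the higher-mortality arm in 5% to 8% of trials (mortality 10% v 15%), 11% to 22% (10% v 20%) and 14% to 38% (20% v 30%). With all randomised patients in the denominator it was 2.5% to 3%.

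**4. Primary outcome, death unrelated to response.** Suppose 60% of survivors respond in both arms and mortality is 20% v 30%. Survivors only shows 60% v 60%. All randomised shows 0.60 × 0.80 = 48% v 0.60 × 0.70 = 42%. Here the arm with more deaths does not look better. The 6-point difference is simply absent from the primary result.

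**5. APACHE II.** Assumed model: baseline N(20, 6); post-treatment score = baseline − 5 + N(0, 5) in both arms; probability of death logistic in the latent post-treatment score with slope 0.15 per point; 100 per arm. The table gives the share of survivor-only t-tests that are significant in favour of the arm with more deaths (nominal 2.5%).

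| Mortality | Raw post-treatment score | Plan's improvement rate, (post − pre)/pre |
|---|---|---|
| 10 points apart (10/20, 20/30, 30/40%) | about 7% to 9% | about 5% to 6% |
| 20% v 35% | about 13% | about 9% |
| 15% v 15% | about 2.6% | about 2.5% |

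The direction is the same on both measures. The effect is smaller on the formula that the plan defines.

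**The case against.** **The text does not say survivors only.** A reader might infer that patients who die cannot be scored at all and that all four outcomes are compared in survivors. The documents do not support that as a statement of fact. No analysis set is named in the article. The lowest grade could take deaths without contradicting its wording. The outcome sections do not tie the after-treatment assessment to day 28, so a last score before death is not ruled out. The grades also refer to an external standard that is not at hand. All of this stands. What remains is that no rule is printed, and the rules that are printed lean towards exclusion.

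**It may be settled elsewhere.** Analysis populations are commonly left to the full protocol or SAP, and that is fair. But the article prints the outcome definitions in full, gives deaths a rule for hospitalization days, and states a final sample net of withdrawals. How death maps onto the primary grade belongs to that definition.

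**Deaths and the withdrawal criteria.** A reader might infer that deaths fall wholly outside these criteria, because death is not listed. That is contestable: criteria 2, 4 and 6 could each capture a patient who goes on to die. On either reading the plan gives such a patient no value on the primary grade.

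**Mortality is reported separately.** An excess of deaths would be seen there, so the harm would not be invisible in the trial as a whole. This stands, but it does not correct the primary result.

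**The sizes are assumed.** This also stands. They show direction and possible scale and do not predict this trial.

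**Worst-rank scoring of CPIS, APACHE II and CT is a choice of estimand.** It mixes mortality into severity measures, and the article gives no CT classification on which to place deaths. This stands, and it limits the fix for these three outcomes.

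**Conclusion.** The concern holds in a limited form. The article defines its primary grade and three secondary measures by a post-treatment assessment, expects deaths, and does not say how they count. Its withdrawal criteria and the final sample of at least 85 per arm point to a completer analysis that would remove deaths from the primary denominator. This is an inference from the text, not a restriction that the text states.

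The bias arises when mortality differs between arms. At assumed mortality of 20% v 30% and equal true response of 40% to 60%, the survivor-only difference is 7.1 to 10.7 points in favour of the arm with more deaths. If death is unrelated to response, the primary comparison shows no difference and the loss is only hidden. In the equal-mortality settings examined there was no distortion. The point should be corrected because the primary result can be misleading in either direction and the remedy is cheap. It does not show that the trial's result will be wrong.

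**What to change.** 1. **Efficacy evaluation criteria in TCM:** add to the lack-of-efficacy grade *or death from any cause before the post-treatment assessment*.
2. **Data analysis:** state that the primary grade is analysed with all randomised patients in the denominator.
3. **Sample size:** state that patients who die count as evaluable for the primary outcome, so that it is clear what the 85 per arm contains.
4. **Secondary outcomes:** for CPIS, APACHE II and CT, label survivor-only comparisons as descriptive and report them beside day-28 mortality. An analysis with death as the worst rank can be added as an optional sensitivity analysis.

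**Cost:** a few sentences and no new data, because day-28 mortality is already collected. The one small downside is that reported efficacy rates become lower in both arms.

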### Secondary outcomes

Clinical pulmonary infection score (CPIS): CPIS is a comprehensive clinical and imaging standard to assess the severity of pulmonary infection. It includes the following indicators: body temperature, white blood cell count, tracheal secretions, oxygenation, X-ray pulmonary infiltration, and progress in etiology. The clinical pulmonary infection score is compared before and after treatment. The CPIS details can be found in Additional file 3. Evaluation of disease severity: the scores of patients in the two groups are compared using the APECHA II scoring system before and after treatment. Improvement rate in APECHA II score = (Post-treatment score − Pre-treatment score)/Pre-treatment score. The APECHAII details can be found in Additional file 2. Clearance of drug-resistant pathogens: observed on days 7, 14, 21, and 28.Comparison of mechanical ventilation time and success rate of weaning off the ventilator are calculated if appropriate.Comparison of mortality: mortality is compared on day 28 between the groups.Radiography indicators: pulmonary CT imaging results are compared between the groups before and after treatment.Number of hospitalization days: survival days of patients who die and hospitalization days of those who survive and are discharged.

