### Randomization and allocation

In each study site, patients with MDRO HAP that fulfill the inclusion criteria and do not meet any of the exclusion criteria are assigned to the trial group or control group according to the corresponding random numbers extracted in the order at visit. Each study site will enroll 40 patients for a total of 200 over the five study sites. A random number table generated using Statistical Analysis Software (SAS), version 9.2, using the randomization method, will be used to assign the participants in a ratio of 1:1, with 100 patients each in the trial group and control group. A researcher will generate the allocation sequence and enroll participants and the clinical researchers will assign participants to interventions. The clinical researchers at each center will provide packaged drugs to the participants according to the randomization number on the packaging; the code labeling will conform to the principles of GCP. The statistician will uncover the blinding as necessary.

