### Statistical analysis

#### Data analysis

The Longhua Hospital Shanghai University of Traditional Chinese Medicine will be in charge of data management and statistical analysis in this study. Statistical analysts are not involved in clinical observation; they are responsible for statistical analysis of study data and timely delivery of statistical reports to the study director. Statistical analysis will be performed with SPSS 20.0 software. Measurement data are expressed as mean ± standard deviation. Normality test and homogeneity test of variance will be performed first. In case of normal distribution and homogeneity of variance, a *t*-test is performed, otherwise a non-parametric test is used. Count data are expressed as frequency constituent ratio (percentage) and *X*^*2*^ test is performed. *P* < 0.05 indicates statistical significance.

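### The APACHE II improvement rate has the wrong sign for a severity score, and CPIS has no stated between-arm comparison (minor; secondary outcomes)

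*Protocol article*

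**What the plan says.** All the outcome wording is in the protocol article, Secondary outcomes.

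- **APACHE II.** The comparison is "Evaluation of disease severity: the scores of patients in the two groups are compared using the APECHA II scoring system before and after treatment". The derived measure follows: "Improvement rate in APECHA II score = (Post-treatment score − Pre-treatment score)/Pre-treatment score".
- **CPIS.** It is introduced with "CPIS is a comprehensive clinical and imaging standard to assess the severity of pulmonary infection". The only comparison given is "The clinical pulmonary infection score is compared before and after treatment".
- **Neighbouring items.** CT findings and day-28 mortality are each said to be compared between the groups.

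Under Primary outcome, the TCM efficacy rate rises with benefit: 90% or more is clinical control and below 30% is lack of efficacy.

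Under Data analysis, the rule for measurement data is "In case of normal distribution and homogeneity of variance, a *t*-test is performed, otherwise a non-parametric test is used". It does not say whether the *t*-test is paired or two-sample, and it names no baseline covariate. The significance level is 0.05, with sidedness not stated.

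**The concern.** Three things stand out, of different weight.

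1. **The formula contradicts its name.** On a severity score a fall is improvement, yet post minus pre is negative when the score falls. Read literally, the arm with the higher improvement rate is the one that did worse. The article then contains two rates that run in opposite directions, with nothing to warn the reader.
2. **CPIS has no treatment contrast.** Both arms receive standard therapy, including antimicrobials, so scores may fall in both. A before/after comparison within an arm measures that fall together with any effect of the decoction. Because the *t*-test is not specified as two-sample, a paired within-arm test is a possible reading.
3. **The baseline score is measured but not used in the named tests.** This does not make them wrong; it gives up precision that costs nothing to keep.

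**Working it through.** **Inputs.** From the article: the formula (Secondary outcomes); 1:1 allocation with 100 per arm (Randomization and allocation); withdrawal below 15% and at least 85 per arm at the end (Sample size); significance at 0.05 (Data analysis). Assumed, because the article gives no value: two-sided testing, a baseline/post correlation *r* of 0.3 to 0.7, equal SDs before and after, and the example scores. That a higher score is worse is inferred from the severity label; the scoring details are in additional files that are not shown.

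**The plan's own figure.** 100 × (1 − 0.15) = 85 per arm. This reproduces.

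**Step 1: sign of the rate.**

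| Pre | Post | As written, (post − pre)/pre | Reversed, (pre − post)/pre |
|---|---|---|---|
| 20 | 12 (better) | −8/20 = −40% | +8/20 = +40% |
| 20 | 20 (same) | 0% | 0% |
| 20 | 26 (worse) | +6/20 = +30% | −6/20 = −30% |

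Reversing the sign of every patient's value reverses the sign of a *t* statistic and the order of the ranks, so a two-sided p-value stays the same. In 4,000 simulated trials of 85 per arm, the largest difference between the two *t*-test p-values was 0.

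As a ratio to baseline, the rate also weights equal changes unequally: a 4-point fall is 4/10 = 40% from a baseline of 10 but 4/20 = 20% from a baseline of 20. That is a reason to keep it for description.

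**Step 2: which contrast is stated.**

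| Outcome | Before/after stated | Between groups stated |
|---|---|---|
| APACHE II | yes | yes |
| CT imaging | yes | yes |
| Day-28 mortality | not applicable | yes |
| CPIS | yes | no |

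To see what a within-arm reading would show, the same simulation gave both arms the same fall of 3 points on a score with SD 5 (0.6 SD), with *r* = 0.5 and no treatment effect. The paired before/after test in one arm was significant in 99.98% of trials. The between-arm *t*-test on relative change was significant in 4.75%, close to the nominal 5%. A significant before/after result is therefore what one expects from recovery alone.

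**Step 3: what baseline adjustment would add.** With the post-treatment SD set to 1, the relative variances are 1 for the post-treatment score, 2(1 − *r*) for the change score and 1 − *r*² for ANCOVA. The difference detectable with 80% power at 85 per arm is (1.96 + 0.84) × √(2 × variance/85).

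| *r* | Variance: post / change / ANCOVA | Detectable difference (SD): post / change / ANCOVA |
|---|---|---|
| 0.3 | 1 / 1.40 / 0.91 | 0.43 / 0.51 / 0.41 |
| 0.5 | 1 / 1.00 / 0.75 | 0.43 / 0.43 / 0.37 |
| 0.7 | 1 / 0.60 / 0.51 | 0.43 / 0.33 / 0.31 |

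At *r* = 0.5, 85 per arm with ANCOVA gives the precision of 85/0.75 ≈ 113 per arm without it. Across this range ANCOVA has the smallest variance of the three.

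**The case against.** The strongest case against has four parts.

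- **The sign is only a label.** The measure is secondary, the primary outcome does not use the formula, the raw scores are collected, and a two-sided p-value is unaffected. A negative rate for recovering patients would soon be noticed. All of this stands and limits the severity. It does not make the formula right: an analysis plan could only contradict it.
- **CPIS is probably meant to be compared between arms.** The trial is randomised with two arms, and the APACHE II and CT items use before/after wording together with a group comparison. That is a fair reading, and nothing in the article says within-arm tests will serve as evidence of effect. The CPIS sentence still leaves the contrast out where its neighbours state it.
- **Covariate adjustment is normally settled in the analysis plan, which is not shown.** This stands. The absence of ANCOVA is not an error here, and the unadjusted between-arm test is valid under randomisation. Adjustment is offered only as an improvement on the test the article names.
- **The size of the gain rests on an assumed correlation.** This stands too, which is why a range is given.

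A reader might also infer that APACHE II, like CPIS, is compared only before against after. The documents do not support that: the article says the scores of the two groups are compared, and the rate is already expressed relative to each patient's baseline.

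**Conclusion.** Minor, confined to secondary outcomes.

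- **Wrong as written:** the APACHE II improvement rate. Its sign contradicts its name and runs opposite to the primary outcome's efficacy rate. The consequence is a misdirected or misread result, not a changed two-sided test. This rests on higher scores meaning greater severity, as the article's own label implies.
- **Incompletely stated:** the CPIS comparison, which names no contrast between arms. A within-arm change could not show an effect of the decoction. It would go too far to say that the trial plans to rely on such tests.
- **Improvable:** the unadjusted test for both scores. ANCOVA would reduce the variance to between 0.91 and 0.51 of that of the post-treatment comparison at assumed correlations of 0.3 to 0.7. It would go too far to call the unadjusted between-arm test invalid.

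**What to change.** 1. Define the APACHE II improvement rate as (pre − post)/pre, or keep the formula and call it relative change with a note that negative values mean improvement. Use it for description.
2. State that CPIS is compared between the trial and control groups, and do not present within-arm before/after tests as evidence of effect.
3. For both scores, preferably compare arms on the post-treatment value by ANCOVA with that score's baseline value as covariate, reporting the adjusted difference with its 95% confidence interval.

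The cost is wording only: the pre- and post-treatment scores are already part of the plan, and no visit, assessment or patient is added. The change should be dated before results are examined by arm.

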Clinical pharmacological studies with *Buzhong Yiqi* decoction have demonstrated that it enhances phagocytosis of the reticuloendothelial system, promotes the non-specific immune function of the body, and has a remarkable inhibitory effect on multi-drug-resistant *Staphylococcus aureus* [17, 18]. This recipe can effectively alleviate inflammatory reactions and boost immunity of the body. Results from previous studies by the authors on *Buzhong Yiqi* decoction for the treatment of HAP, including that caused by MDROs, showed that TCM could significantly relieve the inflammatory reactions of patients, improve clearance of the organisms, shorten the time of mechanical ventilation, and increase the success rate of weaning from the ventilator and had good clinical efficacy. Similar clinical efficacy was observed in other related studies on *Buzhong Yiqi* decoction for the treatment of HAP [19–22]. Therefore, on the basis of previous studies, this study intends to provide an evidence-based rationale and guidance for the clinical treatment of MDRO HAP, further elucidate the scientific notion of “treating different diseases with the same method”, and expand the modern disease spectrum of *Buzhong Yiqi* decoction by performing a multi-center randomized controlled clinical study with *Buzhong Yiqi* decoction (a classical formula for reinforcing healthy *Qi* and eliminating pathogenic *Qi*) in the treatment of MDRO HAP.

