### Inclusion criteria

The eligibility criteria are as follows: (1) patients meet the diagnostic criteria of Western medicine; (2) etiological diagnosis meets the MDRO criteria; (3) aged 40–85 years; (4) patients have signed the informed consent form; (5) Patients also meeting the following criteria as Exclusion criteria, withdrawal/trial discontinuation/drop-out criteria are included into observation.

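### Pathogen clearance is tested by an unadjusted chi-square although the organism should be known before randomisation: a valid test, but one that may give up precision (minor)

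*Protocol article*

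**What the plan says.** Secondary outcomes gives clearance as one undivided item: "Clearance of drug-resistant pathogens: observed on days 7, 14, 21, and 28". It makes no breakdown by species or resistance class.

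Data analysis sets one rule for all categorical outcomes: "Count data are expressed as frequency constituent ratio (percentage) and *X*^*2*^ test is performed". The significance level is 0.05. No stratification or covariate is named.

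Inclusion criteria requires that "etiological diagnosis meets the MDRO criteria". Randomization and allocation puts assignment after eligibility: "patients with MDRO HAP that fulfill the inclusion criteria and do not meet any of the exclusion criteria are assigned to the trial group or" the control group. Allocation is 1:1 within each site in order of visit, and no organism stratum is mentioned.

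Sample size expects 100 enrolled and at least 85 remaining per arm. It states no effect size or power.

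The article nowhere says outright that species are pooled. That follows from reading the undivided outcome together with the single test.

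**The concern.** The trial admits any multi-drug-resistant organism, and clearance may well differ from one organism to another. A factor that predicts the outcome and is fixed before randomisation can be used to sharpen the treatment comparison. Here it needs no new measurement, because an eligible patient must already have an organism identified.

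The unadjusted test leaves that information unused. Two things are at stake. If organisms differ strongly, the test has less power than the same patients could give. And if the arms differ by chance in organism mix, the raw percentages are hard to interpret. Clearance is secondary, but the Discussion names it first among the measures by which efficacy may be confirmed, so it will be read closely.

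**Working it through.** **The plan's own figure.** 100 × (1 − 0.15) = 85 per arm, so the stated 100 enrolled and 85 final agree. No power statement exists to reproduce.

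**Inputs from the article.** 85 per arm; 1:1 allocation; no organism strata; chi-square; alpha 0.05 (two-sided assumed, as the article does not say).

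**Assumed inputs.** Four organism groups and a common odds ratio for clearance of 2.2. Control clearance and group shares are:
- none: 50% in every group, shares 25% each;
- mild: 35, 45, 50, 60%, shares 30, 30, 20, 20%;
- moderate: 30, 40, 55, 70%, shares 35, 25, 20, 20%;
- strong: 15, 35, 60, 85%, shares 35, 25, 20, 20%.

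**Variance that stratifying can remove.** With shares w and clearance p, total variance is P(1 − P), where P = Σwp, and the within-organism variance is Σwp(1 − p). For the strong case P = 0.43 and the total is 0.43 × 0.57 = 0.2451. Within is 0.35 × 0.1275 + 0.25 × 0.2275 + 0.20 × 0.24 + 0.20 × 0.1275 = 0.1750. The ratio is 0.1750/0.2451 = 0.71. The same sum gives 0.2250/0.2480 = 0.91 (moderate) and 0.2405/0.2484 = 0.97 (mild).

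**Chance shift from organism mix.** SD = √(2 × (total − within)/85). Strong: √(2 × 0.0701/85) = 4.1 percentage points. Moderate: √(2 × 0.0230/85) = 2.3. Mild: √(2 × 0.0079/85) = 1.4.

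This shift is part of the ordinary standard error. In the moderate case that is √(2 × 0.248/85) = 7.6 points, and (2.3/7.6)² ≈ 0.09, which is the same 9% of variance found above.

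**Power and type I error.** Simulation of 40,000 trials per scenario and hypothesis, comparing the pooled chi-square (no continuity correction) with the Cochran-Mantel-Haenszel (CMH) test stratified by organism. Site was not modelled.

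| Organism effect | Power, chi-square | Power, CMH | Change in points | Type I error, chi-square | Type I error, CMH |
|---|---|---|---|---|---|
| None | 70.9% | 69.8% | about −1 | 5.4% | 4.9% |
| Mild | 70.2% | 69.7% | −0.5 | 5.4% | 4.9% |
| Moderate | 64.9% | 66.7% | about +2 | 5.2% | 5.0% |
| Strong | 48.0% | 58.1% | about +10 | 5.5% | 5.2% |

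Among the 10% of null trials most imbalanced by organism, the chi-square rejects in 6.4% (mild), 8.3% (moderate) and 16.9% (strong). CMH rejects in 4.9%, 4.1% and 5.2%.

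**Sensitivity with two groups.** In equal groups, clearance of 70% and 30% gives 1 − 0.21/0.25 = 16% of variance removed; 60% and 40% gives 1 − 0.24/0.25 = 4%. With 70% and 30% in an 80:20 mix, P = 0.62 and 1 − 0.21/0.2356 = 11%.

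**The case against.** The strongest objection is that this is detail for the analysis plan. The article condenses a protocol, the plan is not shown, and Data analysis gives generic rules by data type without mentioning clearance. An unadjusted chi-square in a randomised trial is not an error. Much of this stands, and it is why the point is minor. But the article does fix a test for every count outcome and does not mark it as provisional, so it can be commented on as a stated choice. If the analysis plan already stratifies by organism, the point falls away.

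Three stronger readings are tempting, and the documents do not support them.

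- A reader might infer that imbalance in species biases the result on top of the lost precision. It does not: the shift is already inside the standard error, and overall type I error stays near 5%. Rejection exceeds the nominal rate only conditionally, in the trials that turn out most imbalanced.
- A reader might infer that the rationale concerns *S. aureus* alone, since Background says the decoction "has a remarkable inhibitory effect on multi-drug-resistant" *S. aureus*. The same section also claims effects on phagocytosis and non-specific immunity, and better clearance in the authors' earlier pneumonia studies with no species named.
- A reader might also want to adjust for whether the current antibiotic is active against the isolate. Four organism groups crossed with that factor give up to eight strata in about 170 patients (2 × 85). The article does not show that each patient's regimen will be matched to a susceptibility result.

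**Conclusion.** The concern holds as a minor point of efficiency. The stated test for clearance is valid but ignores a baseline factor the trial should already hold. What that costs cannot be fixed from the article, which gives neither clearance rates nor species mix. Under the assumed scenarios, stratifying costs about 1 power point or less when organism matters little or not at all, gains about 2 under moderate differences, and gains about 10 under strong ones. Its other benefit is to keep the result readable if the arms happen to be badly imbalanced by species. All organism shares, clearance rates and the odds ratio of 2.2 are assumptions. That species are pooled, and that the organism is on record for each patient, are inferences from the text.

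**What to change.** Add to Data analysis that clearance is compared with a CMH test stratified by a few broad baseline organism groups chosen by the investigators, for example *S. aureus*, non-fermenters, Enterobacteriaceae and mixed infection. Fix the rule for merging sparse groups before any comparison by arm. Unblinding is a weak cut-off here, because Interventions describes no placebo in the control group. Report the stratified risk difference with its 95% CI and, descriptively, the percentages cleared by organism group and arm.

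The change is to analysis wording: recruitment and treatment are untouched, and the organism is already needed to establish eligibility. The price is about 1 power point if organism does not matter. The percentages by group would also serve the stated aim in Sample size of informing later trials.
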